## Abstract

**Background:**

Dementia care in the Netherlands is shifting from fragmented, ad hoc care to more coordinated and personalised care. Case management contributes to this shift. The linkage model and a combination of intensive case management and joint agency care models were selected based on their emerging prominence in the Netherlands. It is unclear if these different forms of case management are more effective than usual care in improving or preserving the functioning and well-being at the patient and caregiver level and at the societal cost. The objective of this article is to describe the design of a study comparing these two case management care models against usual care. Clinical and cost outcomes are investigated while care processes and the facilitators and barriers for implementation of these models are considered.

**Design:**

Mixed methods include a prospective, observational, controlled, cohort study among persons with dementia and their primary informal caregiver in regions of the Netherlands with and without case management including a qualitative process evaluation. Inclusion criteria for the cohort study are: community-dwelling individuals with a dementia diagnosis who are not terminally-ill or anticipate admission to a nursing home within 6 months and with an informal caregiver who speaks fluent Dutch. Person with dementia-informal caregiver dyads are followed for two years. The primary outcome measure is the Neuropsychiatric Inventory for the people with dementia and the General Health Questionnaire for their caregivers. Secondary outcomes include: quality of life and needs assessment in both persons with dementia and caregivers, activity of daily living, competence of care, and number of crises. Costs are measured from a societal perspective using cost diaries. Process indicators measure the quality of care from the participant’s perspective. The qualitative study uses purposive sampling methods to ensure a wide variation of respondents. Semi-structured interviews with stakeholders based on the theoretical model of adaptive implementation are planned.

**Discussion:**

This study provides relevant insights into care processes, description of two case management models along with clinical and economic data from persons with dementia and caregivers to clarify important differences in two case management care models compared to usual care.

## Background

Dementia is a chronically and devastating disease marked by memory loss and other cognitive impairments as well as behavioural lapses resulting in pronounced consequences for the people with dementia, their families and society. The cost of care for dementia patients, living at home or in a nursing home/home for the elderly, comprised 4.7% (€3.2 billion) of the total health care expenses in 2005 making it one of the most costly diseases in the Netherlands [1,2]. The number of people with dementia is expected to steadily rise due to an ageing population. In the World Alzheimer Report 2009, Alzheimer Disease International estimated that 36 million people worldwide live with dementia, with numbers doubling every 20 years to 66 million by 2030, and 115 million by 2050 [2,3]. The total mean duration of the disease from diagnosis until death was estimated in a large Dutch, prospective, observational analysis of a dementia nursing home cohort to be seven years [4]. Study participants lived in the community for on average five years and then in a nursing home for two years. The median life expectancy from the start of the dementia symptoms varied from 10.7 years for the 65–69 year olds to 3.8 years for those over 90 years old [3]. In a British, population-based cohort of 1304 elderly participants the estimated median survival time from dementia onset to death was 4.1 years for men and 4.6 year for women [5].

In the Netherlands, approximately 70% of the persons with dementia live in the community; a situation that is financially stimulated by current health policies [4,6]. During the course of the disease, persons with dementia become more and more dependent on others, mainly informal caregivers, such as spouses or children. Caring for a person with dementia is a burdensome task for informal caregivers and is associated with more frequent visits to health care professionals and more mental health problems [7-12]. Many services are available to effectively support people with dementia and their caregivers such as several types of daycare and respite care, psychoeducation, discussion groups, telephone support systems Alzheimer cafés and the Meeting centers support programme [13,14]. Specialized home care help to support people with dementia in (instrumental) activities of daily living, memory training and cognitive stimulation. Because of the multiplicity and complexity of problems that persons with dementia and their carers encounter in daily life, comprehensive and combined support programs for persons with dementia and their caregivers were developed in addition to the single interventions. In general, these combined multifaceted support programs are found to be more effective than single interventions in improving the mental health of persons with dementia and/or the carers and in delaying admission to long stay care facilities [15-17]. Furthermore, it is shown that unfulfilled needs of people with dementia are correlated to increased rates of nursing home admission and death [18].

With this wide variety of services available for people with dementia and carers, people often lack information regarding the available services that address their needs and many experience insufficient alignment, management and continuity of care and support during the disease trajectory [19-21]. It is essential to have a strong collaboration between various disciplines in the care and support sector involved in the management of dementia patients. In the past decade, several case management programmes were developed in the Netherlands to address this need. Case management is defined as “a collaborative process in which a case manager assesses, plans, implements, co-ordinates, monitors and evaluates the options and services required to meet an individual’s health, social care, educational and employment needs, using communication and available resources to promote quality cost effective outcomes” [22]. It strives to provide pro-active care coordinated by a case-manager who is supported by a multidisciplinary team of providers of elderly care (e.g. psychologist, geriatrician, general practitioner, neurologist or psychiatrist). The chronic care model (CCM) [23,24] and the guided care model [25] contain quality components that provide a basis for more coordinated care. This is helpful for heterogeneous chronic care trajectories like those found in dementia. Many case management organisations in the Netherlands are modelled after the chronic care model. Models based on CCM consist of a treatment hierarchy starting with specific and anticipatable care for patients with well-defined, uncomplicated problems up to case management which is reserved for patients with highly complex problems who have unpredictable care needs [25]. In this context, it is questionable whether case management is needed for all dementia severity levels. Based on the CCM, healthcare providers should distinguish between more and less complex patients and design cost effective stepped care models including case management for complex cases as recommended by several studies [23,24,26]. This was also demonstrated by Jansen et al. 2011 [27], who found that early detected persons with modest dementia behavioural problems demonstrated no benefit from case management. We aim to generate evidence on the cost effectiveness of case management in comparison with usual care while taking into account levels of behavioural complexity.

Reviews and meta-analyses of case management have yielded inconsistent results on clinical outcomes such as caregiver burden and depression and on economic outcomes [28-31]. Furthermore, only short term effects on caregiver satisfaction were found [32]. Only one meta-analysis including 15 studies found that risk of institutionalization of dementia patients was reduced by multicomponent interventions aimed at caregivers [28]. Based on this meta-analysis, clinicians are advised to tailor interventions according to the specific needs of the individual caregivers and care receivers [28]. Several reviews have indicated that further research should distinguish subpopulations that could benefit from case management [28-30].

In the Netherlands, patients and caregivers are highly satisfied with case management [33]. However, various models of case management are implemented, differing with respect to how services are delivered and by whom, the training provided to its staff and the means of financing. It is unknown whether there are also differences in clinical and cost-effectiveness between these case management models compared with usual care. In the COMPAS study, two different case management models are studied, that is the linkage model and the intensive case management/joint agency model. These models will be compared with usual care and with each other (description in Table 1). These case managements models were chosen based on their emerging prominence in Dutch healthcare for a number of years. The objective of this study is to identify differences in clinical, process and cost outcomes for people with dementia and informal caregivers between the two case management models and the usual care model. Furthermore, the aim is to identify facilitators and barriers in the implementation of the two case management models. This process evaluation focusses on which aspects are successful and their pitfalls.

**Table 1 T1:** Comparison of case management models and care as usual

**Characteristics of different models**	**Linkage Model**	**Intensive Case management/joint agency model**	**Care as usual**
Central point for registration of cognitively impaired	New clients are referred by GP or health specialist to the central registration point	New clients are referred by GP or health specialist to the Multidisciplinary team at central registration point	No
Delivery of services	Independent services and networks	Mainly offered by one organization	Various networks
Possibility to diagnose dementia	By GP or referral to e.g. memory clinic or elderly care physician of mental health care service	By GP or by Multidisciplinary team after referral to central registration point	By GP or referral to memory clinic or elderly care physician of mental health care service
Case manager/dementia nurse	Yes	Yes	nurse present, incidentally
Social psychiatric nurse	No	No	Possible
Multidisciplinary team	External team that case managers can consult as per required	Case manager, elderly care physicians, neuropsychologist, neurologist, geriatrician, psychiatrist, dementia consultant all work within the same organisation as the case managers	No

Our first hypothesis is that in the two case management models the persons with dementia will have less behaviour and mood problems than persons receiving usual care and informal caregivers experience better mental health compared to usual care. Furthermore, we expect a delay in nursing home admission for persons with dementia versus usual care because care needs are better monitored and followed up by services that cooperate within a chain of care. Additionally, an exploratory hypothesis is whether the intensive care/joint agency model is associated with fewer behavioural problems and better follow up care compared to the linkage model, as the services that are part of one organisation may generate more efficiency.

## Methods

### Mixed method study design

A prospective, observational, controlled, cohort design to evaluate clinical and economic effects is accompanied by a qualitative process evaluation for the study on facilitators and barriers of implementation of case management. For the controlled cohort study, dementia care-receivers and their primary informal caregiver in different case management models are compared with those from regions that do not offer case management. The participants are recruited into the study and assessed every six months for two years. The Medical Ethics Committee of the VU University medical center approved the study protocol.

### Care models

The case management models that are key in this study in this project, as well as the care as usual, are described in detail below.

### Linkage model

The linkage model is comprised of independent care agencies where case managers provide the caregiver and patient with informative, practical, and emotional support [34]. In the linkage model, the introduction of case management care starts directly after the patient receives the diagnosis of dementia [35]. The case manager assesses the need for acute help during a telephone intake interview [35]. During an interview at the patient’s home a care and support plan is established that encompasses problems, needs, goals and interventions [22]. Case managers facilitate care by referring patients and their caregivers to various providers of health, social or community care until time of nursing home admission or death of the patient [35]. The case manager implements and monitors the care and support plan under the supervision of an elderly care physician and is in constant communication with the patient’s social system. In addition, during regular meetings with an elderly care physician, guidance is provided for case managers [35].

### Intensive case management model and joint agency model

The second case management model under study is a mix of two existing models: the intensive case management model and joint agency model [34]. Case managers in the intensive case management model guide and support people with dementia for long periods of time and provide care services within one organization [34]. In the joint agency model, the case manager is supported by a multidisciplinary team that includes different health specialists (Table 1) [34]. In this mixed model, the case management process starts with a referral from the general practitioner or a specialist requesting a diagnosis for possible cognitive impairment or (type of) dementia [35]. After the assessment, which is predominantly based on the DSM-IV diagnostic criteria, a care plan is created by the case manager together with the informal care giver(s) and patient [35]. The care plan includes problem and needs areas, intervention possibilities and yearly goals [35]. The care plan is communicated with the general practitioner. Implementation of the care plan is done by the case manager who also monitors it regularly. Like the linkage model, the patient and their family are supported by the case manager until nursing home admission or death of the patient [35].

### Usual care

Care as usual is defined in this study, as “care that is primarily provided or coordinated by the general practitioner and, as a rule, does not include access to a case manager” [36]. Usual care is care according to the guidelines for dementia patients from the Dutch College of General Practitioners [36]. Care may be monitored by a nurse working in general practice in addition to the general practitioner. Patients have access to community services such as home care, day care or meeting centers for people with dementia and their caregivers. A social psychiatric nurse from mental health services is sometimes available for people with dementia that have severe behavioural problems.

### Participants and setting for the controlled cohort study

Pairs of persons with dementia and their primary informal caregiver are included in the study. Persons with dementia are eligible for this study if they live at home, have a diagnosis of dementia, are not terminally-ill, are not anticipated to be admitted to long term care facilities within 6 months, and have an informal caregiver. The informal caregivers are eligible if they are the primary informal caregiver responsible for looking after the patient, have sufficient language proficiency and are not severely ill. Persons with dementia and their caregivers will be recruited from various regions in the North, West and Center of the Netherlands that comprise both rural and metropolitan areas.

### Procedure

The COMPAS study plans to recruit in the experimental group individuals diagnosed with dementia and their caregivers receiving case management from different regional case management models in the Netherlands. Case managers provide lists of patients who are eligible to participate. Potential participants receive written information about the project either via a letter from the research coordinator or via the case manager who approaches them with information directly, asking them if they agree to be contacted by a researcher with more detailed information on the study. Potential participants can either mail (a pre-stamped envelope is attached to the written information) or call the research coordinator or the case manager to let him/her know that they are interested in this additional information. Subsequently, the interviewers call the potential participants to inform them about the study in more detail and to set an appointment for the baseline interview with those who are willing to participate. Interviewers also call participants who have not replied within two weeks after the letter is sent to see if they are interested to participate in the study. For the usual care participants, who do not receive case management, recruitment occurs via outpatient geriatric or neurologic (memory) clinics, Alzheimer centers and general practices where a letter is sent to ask them to participate followed by a phone call from the interviewers to ensure that the letter was received and to provide more information on the study.

Prior to the interviews, all participants will sign an informed consent form. Patients and caregivers are interviewed at their homes by trained research interviewers using case record forms. The cost diary is left at the house, collected during the next interview session, and a new cost diary is provided for the upcoming six months. All outcomes are measured at baseline, 6, 12, 18 and 24 months via questionnaires and interviews. Information on the dementia diagnosis is gathered from the informal caregiver. The caregiver is asked when first symptoms were detected and time of diagnosis. Recruitment started in March 2011. All people currently in case management are screened for eligibility and asked to participate. Data collection is expected to end in 2014.

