### Measuring instruments

#### Primary clinical outcome measures

The primary outcome variables are 1) the frequency and severity of behavioural problems of the person with dementia as assessed by the Neuropsychiatric Inventory (NPI) [37] and 2) psychological stress of the primary informal caregiver as measured by the General Health Questionnaire (GHQ-12) [38]. The NPI includes 12 domains which measure severity (3-point scale) and frequency (4-point scale) of behavioural and psychological symptoms of the patients as well as the emotional impact of the symptoms on the caregivers. Analyses of the psychometric properties of the original ten-item version showed high internal consistency reliability for the frequency*severity product scores (Cronbach’s α = 0.88) and for the specific severity (α = 0.87) and frequency (α = 0.88) ratings [37,39]. The NPI was chosen as the primary outcome in this study because behavioural problems often precede the more relevant cost-carriers like crisis management or institutionalization [40-43] and case management is expected to positively impact behavioural problems and the stress informal caregivers experience. The GHQ-12 was chosen as a primary outcome measure because it is a general measure of mental health and mental health complaints of the caregiver being an important predictor of institutionalization for the person with dementia [40]. The GHQ-12 comprises of three domains: social dysfunction, anxiety and loss of confidence [44]. The scoring method is a four-point response method with excellent reliability (Cronbach’s alpha = 0.90) [44]. Table 2 presents an overview of the primary and secondary clinical outcomes measures for the persons with dementia and their caregivers.

**Table 2 T2:** Outcome measures in the COMPAS study

**Patient**		**Concept**	**baseline**	**6 months**	**12 months**	**18 months**	**24 months**
Primary outcomes	Neuropsychiatric inventory [37]	Behavioural and psychological symptoms *	X	X	X	X	X
Secondary outcomes	Quality of Life in Alzheimer’s Disease [45]	Quality of Life**	X	X	X	X	X
	Short Form-12 [46]	Health related Quality of Life*	X	X	X	X	X
	EuroQol- 5D + C [47]	Health Related Quality of Life**	X	X	X	X	X
	Camberwell assessment of needs for the elderly (CANE) [21,48]	Needs**	X	X	X	X	X
Cost outcomes	Cost diary	Economic evaluation	X	X	X	X	X
	Time between diagnosis and institutionalization	Economic evaluation	X	X	X	X	X

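### The anticipated-admission exclusion is a forecast of a tested outcome, applied through case managers' lists in the exposed groups and with no named assessor in usual care, so the admission comparison can be biased in either direction

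*Protocol article*

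**What the plan says.** The section on participants and setting makes persons with dementia eligible only if, among other conditions, they "are not anticipated to be admitted to long term care facilities within 6 months". This holds for all three groups.

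The Procedure section then gives two recruitment routes. For the case management groups, "Case managers provide lists of patients who are eligible to participate", and the case manager may also approach people directly. Later in that section: "All people currently in case management are screened for eligibility and asked to participate"; this sentence does not name the screener. For usual care, "recruitment occurs via outpatient geriatric or neurologic (memory) clinics, Alzheimer centers and general practices where a letter is sent to ask them to participate"; an interviewer then calls to confirm receipt and give information. The section does not say who judges anticipated admission in usual care.

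The Background states as a hypothesis that "we expect a delay in nursing home admission for persons with dementia versus usual care". Institutionalization is among the secondary outcomes, unplanned institutionalization counts as a crisis, and Table 2 lists "Time between diagnosis and institutionalization" as a cost outcome. The primary outcomes are the NPI and the GHQ-12. Anticipated admission is not among the baseline variables in Table 2.

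**The concern.** Whether an admission is anticipated is a matter of judgement, and the event being judged is one the study hopes to see delayed. In the exposed groups that judgement is built into a list drawn up by the providers under evaluation, who follow the care plan and support the family up to admission. In usual care the people come from other professionals by another route. The same words can therefore remove different shares of imminent admissions from the groups being compared.

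If they do, the groups start follow-up with different near-term admission risk, and the difference appears in the admission results even when case management has no effect. Crises and costs are linked to admission and could shift with it. The safeguards in the Effect evaluation and Discussion sections (propensity scores, a non-responder analysis, interviews with general practitioners on referral) are aimed at referral to case management, severity and low-burden volunteers. None is directed at this exclusion.

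**Working it through.** The article gives no planning figure for admission, so there is none to reproduce. The check asks how large a difference unequal screening alone could produce.

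**Inputs**
- Follow-up: 24 months ("Person with dementia-informal caregiver dyads are followed for two years").
- Admission hazard *h*: assumed constant and equal in all groups, meaning no true effect. The Background cites a mean of five years in the community before the nursing home, so *h* = 1/5 = 0.2 per year; range tried 0.1 to 0.3.
- Detection share *s*: the proportion of people who would be admitted within 6 months and whom the screen removes. The article gives no value, so every *s* below is an assumption.
- Group size 175 and one-sided α = 0.05, borrowed from the NPI calculation in the Sample size section.

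**Formulas at h = 0.2**
- Admitted by 6 months: p6 = 1 − exp(−0.1) = 0.0952.
- Admitted by 24 months: p24 = 1 − exp(−0.4) = 0.3297.
- Person-years at home over 24 months, per person before screening: T = (1 − exp(−0.4))/0.2 = 1.648.
- Part of T contributed by those admitted within 6 months: t6 = (1 − exp(−0.1))/0.2 − 0.5·exp(−0.1) = 0.0234.
- After screening, the 24-month proportion is (p24 − s·p6)/(1 − s·p6), and the admission rate is (p24 − s·p6)/(T − s·t6).

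**Example, 0.5 against 0.25**
- Case management: (0.3297 − 0.0476)/(1.648 − 0.0117) = 0.172 per year.
- Usual care: (0.3297 − 0.0238)/(1.648 − 0.0058) = 0.186 per year.
- Rate ratio: 0.93.

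| s, case management vs usual care | Admitted by 24 months | Rate ratio | Chance of a significant apparent delay |
|---|---|---|---|
| 0.5 vs 0.5 | 29.6% vs 29.6% | 1.00 | nominal |
| 0.5 vs 0.25 | 29.6% vs 31.3% | 0.93 | 10% |
| 0.8 vs 0.4 | 27.4% vs 30.3% | 0.87 | 15% |
| 0.8 vs 0 | 27.4% vs 33.0% | 0.78 | 30% |
| 0.25 vs 0.5 | 31.3% vs 29.6% | 1.08 | bias against case management |

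The last column compares the two 24-month proportions at 175 per group, one-sided 0.05. Across hazards of 0.1 to 0.3, the ratio for 0.8 vs 0.4 is 0.87 to 0.88 and for 0.8 vs 0 is 0.77 to 0.79, so the assumed hazard matters little. The gap between the detection shares drives the result.

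In this model all the distortion falls in the first 6 months. Among people still at home at month 6 the hazard is the same in both groups, so a comparison starting there is unbiased. That relies on the screen removing only people who would have been admitted within 6 months. If it also removes people who would have been admitted somewhat later, some distortion remains.

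**The case against.** Three stronger readings are tempting, and the article does not support them.

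- A reader might infer that usual care is screened by letter, or not at all. The letter is an invitation. The article is silent on who applies the criterion there, and a condensed article may leave that to the full protocol.
- A reader might infer that the bias must favour case management. Case managers plausibly foresee admissions better, but usual care is coordinated by the general practitioner, possibly with a practice nurse monitoring, and recruits partly through general practices. Nothing shows that those clinicians know less about a pending admission.
- A reader might take the extreme case as the likely size. If case managers removed every six-month admission and usual care none, the ratio would be 0.72 (25.9% vs 33.0%). Nothing in the article supports detection of that kind.

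Other objections have weight. The Procedure section says that everyone in case management is screened, so coverage is meant to be complete. The propensity score takes in all variables on which the groups differ at baseline; Table 2 includes the NPI, GHQ-12, ADL and MMSE, and the Discussion adds matching on time since diagnosis and on health. Much of what informs a forecast is therefore measured. The hazard comes from a nursing home cohort, so it describes people who were admitted, and the model ignores death. Table 2 counts time to institutionalization from diagnosis or first symptoms, not from enrolment.

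These points limit the size and remove any claim about direction. They do not remove the stated rule: providers of the evaluated service list who is eligible on a forecast of a tested outcome, and the comparison group is necessarily recruited by other people. Adjustment for correlates of the forecast does not restore the forecast itself.

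**Conclusion.** The concern holds as a risk of bias of unknown direction in the admission comparison. It is more than a missing detail, because following the stated listing rule lets selection that depends on group act on an outcome under test. If there is no true effect and case managers detect imminent admissions better, the illustrative ratios run from 0.93 to 0.78; with the detection shares of the mildest scenario reversed, the ratio is about 1.08. The effect is modest unless usual care screening is nearly absent. All of this rests on assumed detection shares, a constant hazard and no competing deaths.

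Delayed admission is a stated hypothesis but not a primary outcome, and the NPI and GHQ-12 sample sizes are unaffected. Any spill-over to the primary outcomes has not been quantified.

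**What to change.** In the Procedure section, have every recruiting source (case managers, clinics, Alzheimer centers and practices) supply people with a dementia diagnosis who live at home, without applying the admission criterion. Have the research interviewer apply it in all three groups, with one identical question to the caregiver in the call already made before baseline. Log exclusions by group and reason, so that any remaining imbalance can be seen. With equal detection in the groups, the model above gives a ratio of 1.00.

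Recruitment began in March 2011, so this cannot reach dyads already listed. For them, add a sensitivity analysis of admission from month 6 onward among those still at home at month 6.

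The cost is a change in who asks one question, a short log and one extra analysis. There are three downsides. A few more calls will end in exclusion. The month-6 analysis discards early admissions and any early effect, and the Discussion cites a review that found effects mainly in the first year. A question about applications or waiting lists may itself depend on case management, so the question should ask about expected admission in general terms.
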